## Discussion

This will be one of the first studies to evaluate the efficacy of a physical exercise training programme in patients with mild to moderate COPD completely recruited and assessed in primary care. If the results of this study show that this training programme is effective, this would mean a big step ahead in the follow-up of patients with mild to moderate COPD. Patients are actively involved in their disease management in an early phase and the intervention can ameliorate further deterioration and influence their prognosis in the long term [22]. Exercise training has been shown to positively affect some aspects of health status (exercise capacity, muscle force, blood pressure, bone mass) [65]. Using an active lifestyle is necessary to break out of the negative spiral of dyspnoea and deconditioning and is probably essential for a long lasting change in improvements in daily physical activity. The availability of a physical exercise training programme close to the patient’s home most likely improves compliance to the enhanced physical activity [22]. With this enhanced physical activity and the benefits of an improved exercise capacity, a patient can regain his social contacts [22]. This will give a great impact of a patient’s quality of life.

### Bias, confounders and limitations

From a methodological point of view, a cluster randomized design would be the most sound design for the study. The rationale for performing an individually randomized trial is that we observed in a pilot study [44], that physiotherapists were not very keen to deliver a treatment without a proper training programme, although hard evidence of efficacy of a physical exercise training programme COPD was still lacking. Therefore, it would be impossible to recruit sufficient physiotherapy practices with treating *only* control patients. We have found a solution to this problem by allowing the physiotherapist offering the possibility for patients in the control group to participate in the physical exercise training programme after the study-period, in case the intervention has proven to be efficacious. To tackle contamination, we will train and instruct the physiotherapists thoroughly in advance of the study and monitor and instruct them throughout the intervention period. Physiotherapists can only participate if they are willing to deliver both the intervention treatment and sham-treatment. Another strategy to minimize contamination is that patients of the intervention and control group will not be in the same physiotherapy setting at the same time. So, the physiotherapists can focus their mind on just one treatment at the time.

Both the physiotherapists and the patients are not blinded during this study, since they are aware of the treatment procedures. Physiotherapists will conduct the measurements as well as the treatment in patients. Due to practical considerations it is not feasible to perform all measurements in many different practice settings by a single researcher. To assure a high quality and univocal treatment, the participating physiotherapists will be trained and instructed extensively before the start of the training. Also, throughout the intervention period the physiotherapists will be monitored continuously. The researcher will visit the participating physiotherapy practices frequently and will have regular contact by telephone and email in order to check the compliance with the treatment protocols.

As the population in Limburg is the least physically active population of the Netherlands, this might influence the external validity of the study. Another limitation is that the six-minute walk tests are performed on different tracks, which will influence the variability. An advantage of the randomization on patient level instead of physiotherapy practice level is that patients are assigned to smaller and longer passages in a non-differential manner and an equal distribution of patients from the intervention group and control group can be expected per physiotherapy practice. Since we are interested in the difference scores (4 or 6 months minus baseline measurement) and participants are assessed in the same passage on all occasions, we think that the variability is acceptable.

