### Objectives

The primary objective of our study is to evaluate the *efficacy* of a physical exercise training programme (PETP) in patients with mild to moderate COPD in the primary care setting on exercise capacity, physical activity, dyspnoea and quality of life. The 6 month time point is aimed at gaining more insight into the lasting of the effects.

The secondary objective is to assess how patient characteristics and baseline burden of disease modify the effect of a physical exercise training programme on functional exercise capacity in patients with mild to moderate COPD in primary care.

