#### Primary outcome measure

The primary outcome measure will be the functional exercise capacity measured by the increase in the six-minute walk distance (6MWD) at 4 months compared to baseline. The six-minute walk test (6MWT) will be performed in accordance with the ATS Statement: guidelines for the 6MWT [45], except that a standard 30-meter corridor will not always be feasible in a primary care physiotherapy practice, but the minimal track will be 10 meter. The results will be expressed in absolute values and as percent of the predicted value [46]. During the walk test, perceived fatigue and dyspnoea will be measured on a modified Borg scale ranging from zero (nothing at all) to ten (very, very severe) [47]. Oxygen saturation and pulse rate will be measured by a finger pulse oximeter (Onyx 9500) [45].

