### Data analysis

The descriptive characteristics will be presented quantitatively as means (±standard deviation) for continuous variables and as medians for categorical variables and will be presented for the total group, as well as for the separate groups. Unpaired t-tests will be used to compare the effects of the treatment between the intervention group and control group at the end of the physical exercise training programme (4 months). P-values smaller than 0.05 will be considered as statistically significant.

Group (intervention vs. control) by time (pretest vs. posttests) repeated measurements analysis of variance (RM ANOVA) will be performed to examine (1) intervention main effect, (2) time main effect, and (3) intervention by time interaction effect on each of the continuous primary and secondary outcomes. An analysis of covariance will be done to evaluate the relationship between covariates and the dependent variable. The random effect will also be evaluated, since participants from both arms will be nested within the same physiotherapy setting. To evaluate which factors predict a positive outcome, i.e. the physical exercise training programme is effective, a multiple linear regression analysis will be done, using interaction terms between predictors and physical exercise. A predictor variable will make a significant contribution to predicting the outcome when P-value is smaller than 0.05. The following possible predictors are taken into account, baseline: MRC dyspnoea score, walking distance, peripheral muscle strength, level of daily physical activities and compliance with the training programme [62–64].

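### Same-track difference scores justify unequal walk tracks for the primary comparison, but not for baseline walking distance as an effect modifier

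*Protocol article*

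**What the plan says.** All places are in the protocol article.

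- **Primary outcome measure.** The walk test follows the cited guideline with one exception: "a standard 30-meter corridor will not always be feasible in a primary care physiotherapy practice, but the minimal track will be 10 meter". On reporting: "The results will be expressed in absolute values and as percent of the predicted value".
- **Bias, confounders and limitations.** The article concedes that "the six-minute walk tests are performed on different tracks, which will influence the variability". It offers two reasons for accepting this. First, because randomisation is by patient, "patients are assigned to smaller and longer passages in a non-differential manner". Second, "Since we are interested in the difference scores (4 or 6 months minus baseline measurement) and participants are assessed in the same passage on all" three visits, so the variability is judged acceptable.
- **Objectives.** The secondary objective is stated as follows: "to assess how patient characteristics and baseline burden of disease modify the effect of a physical exercise training programme on functional exercise capacity".
- **Data analysis.** This is how that objective is carried out: "To evaluate which factors predict a positive outcome, i.e. the physical exercise training programme is effective, a multiple linear regression analysis will be done", with interactions between each predictor and treatment. The candidate list reads "The following possible predictors are taken into account, baseline: MRC dyspnoea score, walking distance, peripheral muscle strength, level of daily physical activities", followed by compliance with the programme. Just before this, the section says that a random effect will be evaluated because patients of both arms are nested within physiotherapy settings.

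**The concern.** Both reasons for accepting unequal tracks concern the comparison of change between arms. Subtracting a patient's own baseline on the same track removes an additive track effect, and randomisation keeps track length unrelated to arm.

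The effect-modifier regression uses baseline walking distance differently. It compares the level of one patient with the level of another, who may have walked in a different practice on a different track. Nothing is subtracted, so any track effect stays in the predictor. Randomisation does not help either, because the question is whether patients with a low distance respond differently from patients with a high distance, and some of that contrast would be corridor rather than fitness.

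At stake is one of the five listed predictors in a secondary analysis. Its interaction slope would be pulled towards zero and would be harder to read as a statement about baseline burden of disease.

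**Working it through.** **Figures in the plan.** The article gives no figure for the track effect. Its sample size is used below only as an input, and it reproduces: 2 × (1.960 + 0.842)² × 78² / 52² = 35.3, so 36 per arm and 72 evaluable, as stated.

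**Inputs.**
- SD of six-minute walk distance: 62 m (Sample size calculation; six pilot patients in one physiotherapy setting). Because there was one setting, this SD is taken as free of track variation.
- Shift D in measured distance between short and long tracks: not in the documents. Assumed 20, 40 and 60 m. The sign does not matter for dilution.
- Share p of patients on short tracks: not in the documents. Taken as 0.5, which gives the most dilution for a given D, and as 0.2 and 0.1.
- Track length is assumed unrelated to true fitness and to the treatment effect.

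**Formula.** With two track lengths, track adds variance p(1 − p)D² to the predictor. The slope is multiplied by 62² / (62² + p(1 − p)D²), and 62² = 3844.

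| D | p = 0.5 | p = 0.2 | p = 0.1 |
|---|---|---|---|
| 20 m | 3844/3944 = 0.975 (2.5% lost) | 3844/3908 = 0.984 (1.6%) | 3844/3880 = 0.991 (0.9%) |
| 40 m | 3844/4244 = 0.906 (9.4%) | 3844/4100 = 0.938 (6.2%) | 3844/3988 = 0.964 (3.6%) |
| 60 m | 3844/4744 = 0.810 (19.0%) | 3844/4420 = 0.870 (13.0%) | 3844/4168 = 0.922 (7.8%) |

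**Uncertainty in the SD.** Six patients give a 95% interval of about 39 to 152 m under normality. At D = 40 m and p = 0.5, the factor is 1521/1921 = 0.792 (21% lost) at SD 39 m and 23104/23504 = 0.983 (1.7% lost) at SD 152 m.

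**Simulation.** Assumptions: 72 patients in 12 practices, half on short tracks, a true interaction slope of −0.50 m per m, residual SD 70 m, 3,000 runs per setting.

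| D | Slope, no track terms | Power, no track terms | Slope, with track and track-by-arm |
|---|---|---|---|
| 0 m | −0.50 | 0.44 | −0.51 |
| 25 m | −0.48 | 0.42 | −0.51 |
| 50 m | −0.42 | 0.37 | −0.49 |
| 75 m | −0.36 | 0.32 | −0.50 |
| 100 m | −0.30 | 0.29 | −0.51 |

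The mean treatment effect stayed at about 52 m throughout, so the primary comparison is untouched. The track terms bring the slope back to about −0.50 at every D.

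**Random effect for setting.** A random intercept describes practice differences in the outcome. The predictor values, and their product with treatment, still contain the track effect. The article also does not link the random effect to this regression.

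**Percent of predicted.** For levels, an assumed 50 m shortfall lowers the value by 50/700 = 7.1 to 50/500 = 10.0 points at assumed predicted distances of 700 and 500 m. For change, an additive shift cancels: a 52 m gain at 600 m predicted is 52/600 = 8.67 points with or without it.

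**The case against.** The strongest case against the point runs as follows.

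- **The direction and size of the track effect are not in the documents.** The article says only that different tracks influence variability. This stands, so the figures above are conditional, and half the patients on short tracks is the worst mix for a given shift.
- **The consequence is small.** Interaction power is only 0.44 under the simulated assumptions before any track effect, and 0.37 at 50 m with half on short tracks. Track length is not what chiefly limits this analysis. This stands and sets the weight of the point.
- **Practice is considered, and regression detail belongs in an analysis plan.** The random effect shows awareness of clustering, and an article need not list every covariate. That is fair. What remains is that the stated reason for accepting unequal tracks does not extend to an analysis that the same article names.

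A reader might also infer three stronger claims that the documents do not support:

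1. *That the primary result is biased.* It is not. Individual randomisation and same-track differences both protect it.
2. *That short tracks create a false modifier.* This would need treatment effects that vary by practice and go along with track length. Treadmill intensity is tied to the walk-test result, but perceived exertion and dyspnoea also tailor it, the treatment protocol is standardised, and therapists are trained and monitored. Nothing shows such a pattern.
3. *That percent of predicted is a biased analysis.* It is named only as a way of expressing results. No test across practices is planned on it, and an additive shift cancels in its change.

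**Conclusion.** The point holds, and it is minor. The justification for unequal tracks covers the primary comparison but not baseline walking distance used as a level in the effect-modifier regression. If track length affects distance, the interaction slope for that one predictor is diluted: about 2.5% to 19% for shifts of 20 to 60 m with half the patients on short tracks, and about 1.6% to 13% with one fifth. These figures rest on an assumed shift, an assumed mix of two track lengths, an SD from six patients, and independence of track from fitness and treatment effect. The sample size and the primary analysis need no change.

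**What to change.** Record the track length of each practice once. In the effect-modifier regression, add track length and its interaction with treatment beside baseline walking distance and its interaction. Wherever percent-of-predicted levels are reported, state the track length alongside.

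The cost is one number per practice, a sentence of analysis wording, and about two degrees of freedom out of 72 expected evaluable patients. In the simulation with no track effect, power was unchanged at 0.44 with or without the extra terms. No visit, measurement or patient is added. A single linear term for length will leave some track variation in the predictor if the effect of length is not linear. A two-level grouping of track lengths costs the same two degrees of freedom.

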### Potential barriers

From the feasibility study of Faulkner et al. it is known that recruitment of patients with moderate COPD for a physical activity intervention in primary care is very difficult [40]. The reported main recruitment issue for caregivers in that study was lack of available time to participate in research activities [40]. Furthermore, in general practice no objective tool to measure daily physical activity is available, only subjective questionnaires. As a consequence, general practitioners or practice nurses might have a lack of information on this topic and will not consider a follow-up strategy, including referral to a physical exercise training programme.

One of the first major symptoms in COPD is exertional breathlessness. To avoid confrontation with this symptom, patients with COPD are more inclined to adapt their lifestyle, for example taking the elevator instead of climbing the stairs. In this way impairments in daily life are not noticed by the patient. So, on patients’ level it might be a barrier that patients with only a mild airway obstruction and moderate exercise limitation do not feel the need to participate in a physical exercise training programme [66]. In this mild to moderate category, many patients will probably have work commitments and lack of time might be a problem [40].

A key factor in the recruitment of patients is the teamwork between the different healthcare professionals in primary care. From June 2006 till November 2007, our research group has executed an implementation project of physiotherapy for COPD patients in primary care in the region to be studied [44]. One of the main objectives was to start up and improve collaboration between general practitioners, nurse practitioners and physiotherapists. As a result of the project referral policy of COPD patients to physiotherapists in primary care in this region improved. In this way, we expect to minimize recruitment problems.

Given the evidence of the efficacy of pulmonary rehabilitation on functional exercise capacity, dyspnoea and quality of life in patients with moderate to severe COPD, there is now an urgent need to determine whether similar observations apply in the larger group of patients with earlier disease characteristics [40].

## Abbreviations

BMI: Body Mass Index
CCQ: Clinical COPD Questionnaire
COPD: Chronic obstructive pulmonary disease
CRQ: Chronic Respiratory Questionnaire
DTC: Diagnose-treatment combination
FEV_1_: Forced expiratory volume in one second
FVC: Forced vital capacity
GOLD: the Global Initiative for Chronic Obstructive Lung Disease
GP: General practitioner
GPE: Global perceived effect
HRQL: Health Related Quality of Life
MRC: Medical Research Council
NHG: Dutch College of General Practitioners
PAL: Physical activity level
PETP: Physical exercise training programme
PR: Pulmonary rehabilitation
RCT: Randomized controlled trial
ST: Sham-treatment
6MWD: Six-minute walk distance
6MWT: Six-minute walk test.
